### Participants, Interventions, and Outcomes

#### Setting

As Syrian asylum seekers and refugees are dispersed across the United Kingdom, all study activities including recruitment, consent, screening for eligibility, intervention, and interviews will be held on the web to lower barriers to participation. However, access to the intervention could still be influenced by barriers and facilitators associated with its institutional affiliations including the University of Oxford, which will be mentioned on all foreword-facing documents, and those who agree to advertise it to their network.

#### Eligibility Criteria

Inclusion criteria include being a male or female Syrian asylum seeker or refugee in the United Kingdom, aged 18 years and older, and with at least a score of 1 on the Columbia-Suicide Severity Rating Scale (C-SSRS) [38]. Participants also need to be internet literate, have access to a PC or mobile phone with internet, and be willing to provide their email address and the email address of their general practitioner (GP) surgery. Recruitment will take place via the web; and therefore, internet literacy and access also apply. Participants with a score of 4 or above on the C-SSRS, indicating serious SI, will not be eligible to participate. This decision was made to avoid risks of harm to the participants and has thus far not resulted in the exclusion of any participants.

#### Interventions: Description

After providing informed consent and screening for eligibility, baseline measurements of SI, anxiety, depression, and PTSD will be taken for intervention participants. Participants will then receive the 6-week self-help digital intervention via Qualtrics (Qualtrics International Inc), which consists of the following 6 sessions [22]:

Thinking about suicide: The aim of this module is to enable participants to identify the automatic thoughts that give rise to suicidal thoughts in order to gain some control over their thoughts. Specific attention is given to the dichotomous and overgeneralizing nature of the thoughts.Dealing with thoughts and feelings: Participants will learn that they can be resilient in the face of seemingly unbearable feelings. Focus will be given to learning how to tolerate and regulate intense emotions in crisis situations.Thinking about the future: Participants will evaluate their ideas about the future and ask whether they are realistic. Consequently, participants will develop a more realistic view of the future and set new goals.Thinking about the self: Common mistakes in thinking about the self are discussed and challenged. Participants are also taught how to manage suicidality as a long-term vulnerability. Particular attention is given to learning to seek help.Thinking about others: Mistakes in thinking about others will be discussed. Participants will also be provided with information about the effects of suicide for relatives and friends.Repetition and relapse: Several mistakes in thinking and acquired skills are repeated. Attention will also be given to relapse and how to avoid it.

While the intervention was initially intended as a 6-week intervention, it will be provided to participants as a 6-session intervention, which they can complete at their own pace within 6 weeks. Preferably, this involves working on the intervention for 15 minutes daily. If participants fail to submit the session’s homework by the end of each week, a further message will be sent asking if they are having any difficulties or if they want to discontinue their participation. If the participant does not reply within a week, they will be contacted again when it is time to assess their SI as part of the study’s safety protocol. If they do not respond, it will be assumed that they no longer wish to participate. Likewise, any participant who scores 4 or above on the C-SSRS will be excluded from participation [38]. All participants will be encouraged to seek help from their GP or will be provided information about alternative sources of help during the intervention.

While the goal of the study is to track rather than ensure adherence, strategies for improving adherence were one of the main objectives of the cultural adaptation. Specifically, the electronic case tracking form (eCTF) used to track recruitment goals will be used to track the reasons for ending participation throughout the intervention. Adherence rates, in terms of the number of sessions completed and the amount of time taken to complete them, will be assessed during postintervention interviews and with the platform user analytics.

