##### Secondary Outcomes

Secondary outcomes include the feasibility of recruitment goals and measurement instruments. Recruitment goals will be tracked in accordance with the guidelines by Stewart et al [37] for diverse populations. This will include using an eCTF to track the sources of potential participants (NGOs, charities, and social media), the number of participants recruited within the set time period (30 in 6 months), sample characteristics (age, gender, ethnicity, and religion), and reasons for loss at each stage (consent, eligibility, enrollment, etc).

The feasibility of measurement instruments will be assessed in terms of the number of people who completed questionnaires, the amount of information missing, which should not exceed 10%, and the time it took to complete them. This will include measuring SI for intervention participants at baseline (T1), after 3 weeks (T2), and post treatment (6 weeks after baseline: T3). Depression, anxiety, and PTSD will also be measured at baseline and post treatment. If possible, all participants who begin the intervention will complete the follow-up assessment at week 6 irrespective of whether they complete the intervention or not. All the data will be recorded on the eCTF. The outcome measures used in the study are as follows:

SI will be measured using the SI subscale of the C-SSRS, which is a 6-item tool used to assess SI [38], which has shown good internal consistency (α=.966) for an Arabic-speaking population [39]. The C-SSRS was chosen due to its compatibility with Syrian’s conceptualization of SI as a wish for death. An answer of yes to any of the 6 questions indicates a presence of SI, and a score of 4 and above indicates serious SI.

Anxiety and depression will be measured with the Hospital Anxiety and Depression Scale (HADS) [40,41]. The Arabic version has shown acceptable internal consistency for both the anxiety (α=.73) and depression scale (α=.77) [42]. HADS consists of 14 items, which are scored on a 4-point Likert scale between 0 and 3. The total score range is between 0 and 21, with scores between 0 to 7 indicating normal anxiety or depression, scores between 8 to 10 indicating borderline abnormal anxiety or depression, and scores above 11 indicating abnormal anxiety or depression.

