### Participant Timeline

Recruitment will be conducted over a 6-month period starting from February 2024 and ending in July 2024. Recruitment goals will be recorded using the case tracking form up until a final disposition is made. As soon as participants contact OB, they will receive a participant information sheet (PIS) and schedule a time to provide consent. The informed consent process will take 10 minutes via Microsoft Teams, during which the participant will be able to ask questions, and written informed consent can be completed on their behalf. An additional 5 minutes is needed to screen the participant for eligibility. Eligible participants will then complete baseline measures for SI, anxiety, depression, and PTSD, which should take 15 minutes. This entire process should take no longer than 30 minutes. As part of the study’s safety protocol, participants will be contacted at week 3 and 6 to assess their level of SI, which should only take 5 minutes. After 6 weeks, a prearranged web-based meeting will be held via Microsoft Teams to take postintervention measures of SI, anxiety, depression, and PTSD, which should require 15 minutes to complete. Intervention participants will also be sent an email to schedule a date for an interview within 1 week of completing the intervention. The interview will be held via Microsoft Teams, which should take 45-60 minutes to complete.

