#### Data Collection Plan: Retention

##### Participant Retention

To enable retention, obtaining informed consent, eligibility screening, enrollment, and all outcome measures will be completed via Microsoft Teams with the assistance of OB instead of web-based surveys. Participants will be followed throughout the trial, and reasons for nonadherence and withdrawal will be recorded within the eCTF if possible. As mentioned earlier, the intervention has been culturally adapted to improve engagement and understanding [2].

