##### Data Management

Original written informed consent forms and outcome measures completed by OB on behalf of the participant will be scanned, and password-protected copies will be sent to the participant via email. These data as well as eligibility screening and data necessary to stratify the postintervention interviews such as ethnicity, gender, and religion will be entered electronically into individual case tracking forms labeled with a unique participant number and held in OneDrive for Business provided by the university. Data from eCTFs will later be added to a joint database for analysis once the participant reaches a final outcome. Interview participants’ audio recordings will be labeled with a unique participant number and stored on OneDrive for Business. They will then be deleted after their transcriptions and translations are uploaded to OneDrive. Participant contact details connected to their unique participant number will be kept in a form on OneDrive for Business throughout their participation and deleted when they reach a final outcome. Access to the uploaded data will only be permitted for the DPhil researcher (OB) and the principal investigator (KB) and upon request to members of the Medical Sciences Interdivisional Research Ethics Committee for the purposes of monitoring and auditing of the research. In accordance with university policy, all nonidentifiable data will be stored for at least 3 years after publication. At the end of the study, OB will transfer all data from university servers to the custodianship of the principal investigator (KB), who will thereon be responsible for data management.

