### Monitoring

#### Harms

The intervention was previously found to be safe for general populations in the Netherlands [24], Belgium [25], and Australia [26] and Turkish immigrants in the Netherlands and the United Kingdom [22]. A safety protocol developed in collaboration with and approved by the university ethics department will ensure the safety of participants throughout the study. The safety protocol has an important balance to make between minimizing the risk of adverse events while still ensuring that the intervention is provided to populations that are most likely to use it. As such, Syrian asylum seekers and refugees in the United Kingdom who have serious SI will not be allowed to participate. After providing consent, participants will be assessed for suicidal thoughts using the SI subscale of the C-SSRS [38]. An answer of yes to any of the 6 questions indicates a presence of SI and a score of 4 and above indicates serious SI, specifically, active SI with some intent to act. Participants who answer yes to any of the questions will be encouraged to contact their GP and will be provided with information about alternative sources of help. In addition to measuring SI before receiving the intervention (T1: baseline), SI will be measured again at T2 (week 3) and T3 (week 6). Any increase in SI will be reported to the principal researcher (KB), who will review the circumstances and act according to his judgment. If a participant scores above the cutoff score (4 and above) during the web-based meeting, they will be immediately encouraged to seek help from their GP or their GP surgery will be contacted with a generic email already approved by the ethics committee, and they will be withdrawn from the study. Participants will be informed about this procedure in the PIS.

The DPhil researcher (OB) will also report any incidental findings to the principal investigator (KB), who will in turn review the circumstances and act according to his judgment. If further steps are necessary, the matter will be referred to the Multi-Agency Safeguarding Hub, which will be made within 1 working day of first receiving the information from the participant. The Local Area Designated Officer will then advise on the next appropriate steps to take. If any risk of harm is directed toward an adult, a referral will be made to the relevant statutory agency. If there is a risk of immediate harm, the emergency services will be contacted via 999.

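### Silence at the next suicidal-ideation check is presumed to be withdrawal, about three weeks before T3 for early non-responders, and the article states no action for a missed check

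*Protocol article*

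**What the plan says.** The rule is in the Protocol article, Interventions: Description. It has three steps: homework not submitted by the end of a week, no reply within a week to a message asking about difficulties or a wish to stop, then a further contact when SI is next due to be assessed. That contact is described as belonging to the safety protocol. The outcome of silence at that point is: "If they do not respond, it will be assumed that they no longer wish to participate". The rule names no particular week.

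Other sections bear on it:

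- Participant Timeline fixes the checks: "participants will be contacted at week 3 and 6 to assess their level of SI".
- Secondary Outcomes, with the qualifier that it applies where possible, says that "all participants who begin the intervention will complete the follow-up assessment at week 6 irrespective of whether they complete the intervention or not". It also sets a limit for the measurement instruments: "the amount of information missing, which should not exceed 10" per cent.
- Participant Retention states: "Participants will be followed throughout the trial".
- Harms gives the SI-based safety triggers: "Any increase in SI will be reported to the principal researcher", and "If a participant scores above the cutoff score (4 and above) during the web-based meeting" the participant is urged to see the GP, or the GP surgery is emailed, and the participant is withdrawn. Incidental findings and known risks of harm have their own routes.
- Eligibility Criteria requires a C-SSRS score of at least 1 and excludes scores of 4 or above.
- Participants are encouraged to contact a GP or are given other sources of help, whatever happens later.

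**The concern.** Three things are at stake.

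**Follow-up.** The rule can close a participant's record at week 3. T3 is the only post-treatment measurement of depression, anxiety and PTSD, and the plan wants it for non-completers too. Interventions: Description does not say that week 6 is still attempted after silence at week 3.

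**Safety.** Every enrolled participant had SI at entry. Silence may mean that the person has left, or that the person is worse. Each route under Harms starts from something learned about the participant, and someone who cannot be reached supplies nothing. In the article, the only stated consequence of a missed check is presumed withdrawal.

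**Meaning of the record.** Reasons for ending participation go into the eCTF and feed the qualitative assessment of suitability, part of the primary outcome. Taking silence as a wish to leave supplies a reason that nobody gave.

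**Working it through.** The plan gives no figure of its own on this point, so the check is a timeline followed by an item count.

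**Timeline.** Inputs: weekly homework deadline and one-week reply window (Interventions: Description); SI checks on days 21 and 42 (Participant Timeline, Secondary Outcomes). For homework missed at the end of week w, the reply window closes on day 7w + 7, and the next check is the first of days 21 and 42 not before that.

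| Homework first missed, week | Reply window closes | Next SI check | Days before T3 |
|---|---|---|---|
| 1 | day 14 | day 21 | 42 − 21 = 21 |
| 2 | day 21 | day 21 (boundary) or day 42 | 21 or 0 |
| 3 | day 28 | day 42 | 0 |
| 4 | day 35 | day 42 | 0 |
| 5 | day 42 | day 42 | 0 |

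The rule therefore puts T3 at risk only for those silent after week 1, possibly week 2. For anyone first silent from week 3 on, the next check is T3 itself and no attempt is lost.

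**Safety routes.** The triggers under Harms are an increase in SI, a score of 4 or above, an incidental finding, or a known risk of harm. All need information from or about the participant. None is triggered by failure to make contact.

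**Missing information.** The 10% limit applies to information, so items are the natural unit. Inputs from Secondary Outcomes: C-SSRS SI subscale 6 items, HADS 14, PCL-5 20.

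- T1: 6 + 14 + 20 = 40. T2: 6. T3: 40. Total per person: 86.
- Early silence with no T3 loses 6 + 40 = 46 items. The 6 at T2 are lost whatever the rule; the 40 at T3 are what the rule puts at risk (40/86 = 46.5% of that person's items).
- For the target of 30: 30 × 86 = 2580 items.

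| Early-silent of 30 | Missing if T3 is lost | Missing if every T3 is recovered |
|---|---|---|
| 4 | 184/2580 = 7.1% | 24/2580 = 0.9% |
| 5 | 230/2580 = 8.9% | 30/2580 = 1.2% |
| 6 | 276/2580 = 10.7% | 36/2580 = 1.4% |

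Assumption: no other items are missing. On the 16 enrolled so far (16 × 86 = 1376 items), 3 early-silent would give 138/1376 = 10.03%.

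**How many there are.** The documents give no rate. Of 16 enrolled, 12 had completed the postintervention interview, so at most 16 − 12 = 4 can have been presumed withdrawn by then. The range is 0 to 4: those four may still have been in follow-up, or not interviewed because 12 was the planned number of interviews. The share who would answer at week 6 is also unknown, anywhere from 0% to 100%.

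**The case against.** The strongest reply is that this is a condensed article. The ethics-approved safety protocol is a separate document, and how a missed safety call is handled is what such a document would contain. This stands: the point can only be about the rule as printed. Even so, the article does describe this contact as a safety step and does say what follows silence, so the printed rule is worth putting right.

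Second, Interventions: Description never cancels the week-6 contact, Participant Timeline schedules it with no exception for non-responders, and Secondary Outcomes wants it where possible. The rule can be read as ending the intervention while follow-up continues. This also stands, and rules out calling the sections contradictory. That both readings are open is the reason to settle it in one sentence.

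Third, the eCTF records reasons for non-adherence and withdrawal where possible, and the first message asks about difficulties. That helps for anyone who replies. For someone who never does, the assumption is all that remains.

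Fourth, stopping after repeated unanswered contacts respects the right to leave at any time, and the article reports that people in the earlier study avoided NHS help partly out of fear for their asylum application. This is a fair cost of the change, and it is why a single further attempt is enough.

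A reader might also infer that contact details would be erased before week 6, since Data Management keeps them "throughout their participation and deleted when they reach a final outcome". The documents do not support that as a finding. They do not say whether presumed withdrawal is a final outcome, and Participant Withdrawal is worded for people who choose to discontinue.

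**Conclusion.** The point holds as a cheap improvement to an operative rule. For participants silent after week 1, possibly week 2, withdrawal is presumed about three weeks before T3. This is in tension with the aim of assessing all starters at week 6 and with following participants throughout, and the article states no action for a missed SI check in a sample that all had SI at entry.

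Two stronger readings should not be drawn. One is that the plan leaves silent participants without safety cover: the full safety protocol is not shown and may deal with it, scores of 4 or above are excluded at entry, and general advice on sources of help is given. The other is that the rule breaks the 10% limit. Percentages of persons without T3 do not test that limit, because Secondary Outcomes lists the number of people completing questionnaires separately from the amount of information missing. By item, 4 early-silent of 30 stays within it at 7.1%; 6 of 30 are needed to exceed it. With no rate of early silence in the documents, no breach is shown. The size of the benefit depends on that rate and on how many would answer at week 6, both unknown.

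**What to change.** - **Interventions: Description.** Treat silence at week 3 as stopping the intervention only. Code it in the eCTF as lost to contact, not as a wish to leave. Still make the scheduled week-6 contact once, unless the person has said that they want to leave; such people are withdrawn as now and not contacted again.
- **Participant Withdrawal and Data Management.** State that contact and GP details of those lost to contact are kept until the week-6 attempt is closed, then deleted as now.
- **Harms.** Report each missed SI check to the principal investigator, who acts on judgement as already provided for an increase in SI.

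For those first silent from week 3 on, only the coding and the missed-check report apply.

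The cost is wording in these sections, one eCTF code, a minor ethics amendment and at most one line in the participant information sheet. It needs no new assessment, staff or score threshold. The downside is one possibly unwanted message per early-silent participant, with details held up to three weeks longer. At the time of the article's Results, the contact rule could still reach at most the 4 enrolled participants without an interview and the 30 − 16 = 14 yet to enrol.

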#### Outcomes

##### Primary Outcomes

The primary outcomes of the study include the acceptability and suitability of the intervention to Syrian asylum seekers and refugees in the United Kingdom with SI. The acceptability of the intervention to participants will be assessed during interviews in terms of cultural relevance (ie, the familiarity of the therapeutic content to one’s cultural background and lived experiences with the migratory process), cultural appropriateness (ie, appropriateness of the therapeutic content in terms of the Syrian cultural context), and whether participants were satisfied with their experience [22].

The suitability of the intervention will be analyzed quantitatively in terms of recruitment and adherence rates. Recruitment rates will be assessed in terms of the percentage of those contacted who met the eligibility criteria and the percentage of those eligible who were enrolled, which should be 70% at each stage. Adherence rates will be assessed in terms of the number of sessions attended, which should be at least 70%, and the time spent completing them. The suitability of the intervention will also be assessed qualitatively in terms of the barriers and facilitators of engagements by way of the case tracking form and postintervention interviews.

##### Secondary Outcomes

Secondary outcomes include the feasibility of recruitment goals and measurement instruments. Recruitment goals will be tracked in accordance with the guidelines by Stewart et al [37] for diverse populations. This will include using an eCTF to track the sources of potential participants (NGOs, charities, and social media), the number of participants recruited within the set time period (30 in 6 months), sample characteristics (age, gender, ethnicity, and religion), and reasons for loss at each stage (consent, eligibility, enrollment, etc).

The feasibility of measurement instruments will be assessed in terms of the number of people who completed questionnaires, the amount of information missing, which should not exceed 10%, and the time it took to complete them. This will include measuring SI for intervention participants at baseline (T1), after 3 weeks (T2), and post treatment (6 weeks after baseline: T3). Depression, anxiety, and PTSD will also be measured at baseline and post treatment. If possible, all participants who begin the intervention will complete the follow-up assessment at week 6 irrespective of whether they complete the intervention or not. All the data will be recorded on the eCTF. The outcome measures used in the study are as follows:

SI will be measured using the SI subscale of the C-SSRS, which is a 6-item tool used to assess SI [38], which has shown good internal consistency (α=.966) for an Arabic-speaking population [39]. The C-SSRS was chosen due to its compatibility with Syrian’s conceptualization of SI as a wish for death. An answer of yes to any of the 6 questions indicates a presence of SI, and a score of 4 and above indicates serious SI.

Anxiety and depression will be measured with the Hospital Anxiety and Depression Scale (HADS) [40,41]. The Arabic version has shown acceptable internal consistency for both the anxiety (α=.73) and depression scale (α=.77) [42]. HADS consists of 14 items, which are scored on a 4-point Likert scale between 0 and 3. The total score range is between 0 and 21, with scores between 0 to 7 indicating normal anxiety or depression, scores between 8 to 10 indicating borderline abnormal anxiety or depression, and scores above 11 indicating abnormal anxiety or depression.

PTSD will be measured with the Arab versions of the Posttraumatic Stress Disorder Checklist for *DSM-5* (*Diagnostic and Statistical Manual of Mental Disorders* [Fifth Edition]; PCL-5), which has shown high (α=.85) internal consistency [43]. The scale consists of 20 self-report items. Each item includes 5 points with scores ranging between 0=not at all and 4=extreme. A total score of 31-35 or higher suggests that a patient may benefit from PTSD treatment.

